#### 4.6 Rationale:

Our intention is to seek licensure of Euvichol-Plus in India, which is being manufactured under PIC(S) GMP in Korea by EuBiologics. Vaccine has been registered in multiple countries, with WHO Pre-qualification for use in subjects 1 year and above. Euvichol-Plus has been procured from UN agencies, comprising more than 70% of OCV supply to cholera endemic countries worldwide. Proposed registration study in India will allow use of new Euvichol-Plus in India which is similar in composition to Shanchol but come in a single use plastic tube presentation, for easy administration.

#### 4.7 Study Objectives

##### Primary:

- To evaluate the immunogenicity of Euvichol-Plus in healthy adults and children as compared to WHO prequalified comparator Oral Cholera Vaccine Shanchol

##### Secondary:

- To evaluate and compare the safety of Euvichol-Plus with Shanchol in healthy adults and children.

#### 4.8 Study Endpoints:

##### Primary immunogenicity endpoint:

Assessment of seroconversion rate

- The proportion of subjects with at least 4 times higher anti-*V. cholerae* O1 Ogawa and Inaba antibody titer at 2 Weeks after the second dose (Visit 2) as compared to baseline titers prior to investigational product dosing (Visit 1).

##### Secondary immunogenicity endpoints

- The proportion of subjects with at least 4 times higher anti-*V. Cholerae* O139 antibody titer at 2 Weeks after the second dose (Visit 2) as compared to baseline titers prior to investigational product dosing (Visit 1).

- Geometric Mean Titer (GMT) and Geometric Mean Ratio (GMR) as measured by anti-V. *Cholerae* O1 Ogawa and Inaba antibody titer at 2 Weeks after the second dose (Visit 3) as compared to baseline titers prior to investigational product dosing (Visit 1).
- Geometric Mean Titer (GMT) and Geometric Mean Ratio (GMR) as measured by anti-V. *Cholerae* O139 antibody titer at 2 Weeks after the second dose (Visit 3) as compared to baseline titers prior to investigational product dosing (Visit 1).

**Safety endpoints:**

- Solicited adverse events (Day 0 ~ 3) and Unsolicited adverse events (Day 0 ~ 28) including abnormal vital signs and physical examination.
- SAE (Day 0 ~ 28) including abnormal vital signs and physical examination.

**5.0 HANDLING, STORAGE, DISPENSING AND ACCOUNTABILITY PROCEDURES FOR INVESTIGATIONAL PRODUCTS**

**5.1 Investigational Product Receipt and Storage**

Sponsor should supply sufficient quantity of investigational products, for administration to subjects as well as retention purpose. The investigational products should be supplied in sealed packages with appropriate label and certificates of analysis. These investigational products will be kept under controlled access at CRO

The investigational vaccines will be stored under controlled conditions at 2-8°C.

The clinical study material for the study must be used in accordance with the protocol.

The following information will be displayed on dispensing/dosing label prepared for this study (Not limited to):

- Randomization number
- Visit number
- Route of administration
- Storage details
- Batch Number
- Manufacturing date
- Expiry date
- For clinical trial purpose only

## **5.2 Dosing & Dispensing**

1.5 ml/dose which will be administered on Day 0 and Day 14.

## **5.3 Follow-up**

Follow-up is planned for a period of 2 weeks after each vaccination.

## **5.4 Subjects Compliance**

Window period of +3 days will be allowed for visit 2, and visit 3. Subjects not reporting to the hospital or reporting late by more than 3 days for second dose of vaccination or post vaccination follow-up visit after second dose will be excluded from immunogenicity analysis. All the subjects receiving at least 1 dose will be included in safety analysis.

## **5.5 Study Product Accountability**

The principal investigator shall keep and maintain complete and accurate records of investigational material. Records showing the receipt and disposition of all materials shall include an IP accountability log and vaccine administration log. An IP accountability log shall include date on which shipment was received, batch no., manufacturing and expiry date. Vaccine administration log shall include enrollment ID, product arm, date and time of vaccination and identification of vaccine administrator. All unused investigational medication will be returned to the Sponsor with proper records. Applicable SOPs as per sponsor norms shall be followed thereafter.

## **5.6 Concomitant vaccines**

No concomitant vaccination will be allowed during the study period.

## **5.7 Concomitant Medication**

All concomitant medication, including non-study medicines, being taken by the subjects at enrolment and during this clinical trial are to be regarded as concomitant medications and must be documented on the “Concomitant Medications Record” section of CRF.

Antipyretic medication (Paracetamol) may be administered in case of fever, but prophylactic use of antipyretic medication is not permitted. In case if any other medication is administered to the subject during the course of the study, the decision to continue or discontinue the subject in the study would be taken by the investigator in consultation with sponsor. The decision would be based on whether the administered medication is known to interfere with the immune response.

The following concomitant treatments are discouraged and, if used, will lead to subject's withdrawal during this study (see exclusion criteria as well):

1. Systemic steroids
2. Other immune-suppressive agents
3. Blood or plasma derivatives including immunoglobulin.

## **6.0 STUDY DESIGN**

### **6.1 Description of Study Design**

Open Label, multi-centric, randomized, parallel group, comparative study. The purpose of this study is to assess and compare the Immunogenicity and safety of Euvichol-Plus with Shanchol vaccine in aged 1 and above, in Indian population.

#### **DSMB**

There will be a DSMB meeting which will analyze the 14 days post vaccination safety data of the subjects of the cohort 1 accordingly give its recommendations for the enrollment of cohort DSMB will also review the 14 days post vaccination safety data of the subjects of cohort. Subsequent, DSMB meeting will take place as required.

### **6.2 Sample Size**

A total of 416 eligible subjects will be enrolled at visit 1 for the study as per below

#### **Cohort 1 adults:**

Test: 104 subjects

Reference: 104 subjects

#### **Cohort 2 children:**

Test: 104 subjects

Reference: 104 subjects

Total Sample size with 10% Dropout is 416. As per published clinical study evaluating immunogenicity of Shanchol and Euvichol, the seroconversion rates (4-fold rise in antibody titres) 14 days after first and second dose of vaccine ranges from 73% to 90% in adults and children. Assuming seroconversion rate of 70% in the reference arm, power of 90%, alpha of 5% (2-sided) and a non-inferiority margin of 10%, 186 subjects would be required in the test and reference arms to establish non-inferiority of the vaccine.

Considering a dropout rate of 10%, a total of 416 subjects will be enrolled in the study (208 in Test and 208 in reference arms).

Approximately 208 subjects enrolled in the study will be adults ( $\geq 18$  to 60 years of age) while remaining 208 would be children ( $\geq 1$  to  $<18$  years of age).

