| Sample Size Justification | 
Total Sample size with 10% Dropout is 416.
 
As per published clinical study evaluating immunogenicity of Shancol and Euvichol, the seroconversion rates (4-fold rise in antibody titres) 14 days after first and second dose of vaccine ranges from 73% to 90% in adults and children.
 
Assuming seroconversion rate of 70% in the reference arm, power of 90%, alpha of 5% (2-sided) and a non-inferiority margin of 10%, 186 subjects would be required in the test and reference arms to establish non-inferiority of the vaccine.
 
Considering a dropout rate of 10%, a total of 416 subjects will be enrolled in the study (208 in Test and 208 in reference arms).
 
Approximately 208 subjects enrolled in the study will be adults (<math>\geq 18</math> to 60 years of age) while remaining 208 would be children (<math>\geq 1</math> to <math><18</math> years of age).
                                                                                                                                                                                                                                                                                                                                                                                                                                                                       |

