To ensure the reformulated vaccine could be made available internationally, IVI facilitated a technology transfer between VaBiotech and Shantha Biotechnics Ltd., a private biotech company in Hyderabad, India (acquired by Sanofi in 2009), a country with a national regulatory authority certified as fully functional by WHO. In parallel with the technology transfer, IVI, in collaboration with India's National Institute of Cholera and Enteric Diseases (NICED), conducted a cluster-randomized, placebo-controlled efficacy trial with the reformulated vaccine in Kolkata, India. The two-dose vaccine was shown to provide a protective efficacy of 65% for at least 5 years and this was the first ever demonstration of strong sustained protection by an oral cholera vaccine. In 2009, the vaccine was licensed in both Vietnam (mORCVAXTM) and India (Shanchol), and in 2011, Shanchol was approved by the WHO Prequalification. Several clinical trials have been done on Shanchol vaccine in India in past as summarized below;

- **Immunogenicity study of OCV, Kolkata, India (NCT00419133):**

An open label randomized, placebo-controlled trial was conducted to assess the immune responses following one and two doses of the bivalent killed, whole-cell, oral cholera vaccine among adults and children in Kolkata, India. The study assessed whether receipt of a single dose of OCV is as immunogenic as receipt of two doses among adults and children residing in cholera-endemic areas in Kolkata. In addition, the safety of the OCV was also assessed after each dose. The rates of seroconversion after the second dose were found to be 46% of adults and 82% of children.

- **Study on dose-flexibility of OCV, Kolkata, India (NCT 01233362):**

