The objective of this trial was to compare safety and serum vibriocidal antibody responses in participants receiving two OCV doses either 14 days or 28 days apart. It was a double-blind, RCT conducted at the Clinical Trials Unit of the National Institute of Cholera and Enteric Diseases (NICED). Participants were stratified by age group (1–5y, 6–10y, 11–17y, and ≥18y). A total of 356 participants (178 children, 178 adults) were recruited. No statistically significant difference was noted between intervention arms in seroconversion or geometric fold rise. The GMF rise from baseline was higher for O1 Inaba in adults, after receipt of the first dose (6.8 and 8.9 respectively in the 14- and 28-day interval arms) compared to receipt of the second dose (4.6 and 4.7 respectively). In children, the responses were more pronounced with GMF rise from baseline after first dose in both the arms being 29.7 and 20.8 respectively. The GMF rise after second dose was 17.5 and 10.7 respectively

- **Non-inferiority trial on vibriocidal response, Kolkata, India (NCT01579448):**

A nested, open-label controlled trial of OCV was conducted among healthy non-pregnant subjects aged 6–14 years and >15 years who were initially immunized with two doses of vaccine or placebo five years before as part of a large randomized controlled trial of an oral cholera vaccine. All participants who were in the placebo arm of the phase III efficacy trial were scheduled to receive two doses of vaccine at the end of the trial period. Since unbinding was performed to conduct analysis and identify all individuals who needed to be given the vaccine, an open label trial design was employed in this study. Seroconversion rates were 66% and 69% following two-dose regimens in the boosting and primary immunization arms (boosting arm was non inferior to primary immunization arm). Seroconversion rate was 71% following one-dose regimen in boosting arm and was non inferior to two-dose regimens in the primary immunization arm. When comparing the immune responses between young children (6–14 years) with older children and adults (>15 years), there was no significant difference in the geometric mean fold rise or the percentage who seroconverted in each intervention arm following two doses of OCV.

- **Safety and Immunogenicity of OCV, Vellore, India (NCT00760825)**

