This is open-label study to assessed the safety and immunogenicity of two doses (14 days apart) of an indigenously manufactured, killed, bivalent (*Vibrio cholerae* O1 and O139), whole-cell oral cholera vaccine in healthy adults (n = 100) and children (n = 100) in a cholera endemic area (Vellore, South India) to fulfill post-licensure regulatory requirements and post-World Health Organization (WHO) prequalification commitments. This study was an open-label, post-licensure, mono-center trial in healthy adults aged 18–40 years and children aged 1–17 years. No serious adverse events were reported during the study. Commonly reported solicited adverse events were headache and general ill feeling. Seroconversion rates after the first and second dose in adults were 67.7% and 55.2%, respectively, against O1 Inaba; 47.9% and 45.8% against O1 Ogawa; and 19.8% and 20.8% against O139. In children, seroconversion rates after the first and second dose were 80.2% and 68.8%, respectively, against O1 Inaba; 72.9% and 67.7% against O1 Ogawa; and 26.0% and 18.8% against O139. The geometric mean titers against O1 Inaba, O1 Ogawa, and O139 in both adults and children were significantly higher after each vaccine dose compared to baseline titers (P < 0.001; for both age groups after each dose versus baseline). The seroconversion rates for O1 Inaba, O1 Ogawa, and O139 in both age groups were similar to those in previous studies with the vaccine.

In conclusion, the killed, bivalent, whole-cell oral cholera vaccine has a good safety and reactogenicity profile, and is immunogenic in healthy adults and children.

In addition, IVI reached out to several Developing Countries Vaccine Manufacturers (DCVMs) for technology transfer and product development partnerships, and transferred OCV technology to EuBiologics Co., Ltd in South Korea. After the lab scale technology transfer IVI and EuBiologics initiated the research and development for fed batch production and in February 2011, EuBiologics successfully scaled up the process to manufacturing scale (30 L fermentation) and in December the same year to 100 L fermentation.

Preclinical toxicity studies were conducted in early 2011, and by September 2012, a phase I study was initiated by EuBiologics in Korea. In February 2013, the study was completed, confirming that their killed whole-cell OCV was safe, well-tolerated, and immunogenic.

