The phase I results enabled EuBiologics to proceed with a randomized controlled phase III trial to assess the safety and immunogenicity of their vaccine as compared to Shanchol. This trial was conducted in the Philippines and immunogenicity testing was performed at the IVI labs in Seoul. The clinical study was completed in August 2014, and demonstrated that two doses of the EuBiologics' vaccine induced vibriocidal responses comparable to those elicited by Shanchol. Based on these results, an export-only licensure application was submitted to Korea's Ministry of Food and Drug Safety (MFDS) in September 2014, and in January 2015 the vaccine (Euvichol-Plus) was approved.

In late January 2015, EuBiologics, submitted a dossier for WHO prequalification. By the end of the year, Euvichol-Plus was WHO-prequalified, making it the second vaccine from the IVI pipeline to be WHO-prequalified. This formulation of Euvichol-Plus was produced in a 100-liter fermenter, giving a production capacity of approximately 6 million doses per year. The company continued to make improvements to the vaccine. In 2014, EuBiologics increased production capacity by investing in a 600-liter fermenter and scaling up to enable production of up to 25 million doses per year by 2018. It also slightly changed the formulation by removing thimerosal, which was considered unnecessary in a single dose oral vaccine. This new variation of Euvichol-Plus obtained WHO prequalification in September 2016.

To further improve Euvichol-Plus, EuBiologics changed the presentation of the vaccine from conventional glass vials to plastic tubes (Euvichol-Plus, also thimerosal free), to facilitate delivery in emergency situations or humanitarian campaigns. The new plastic packaging of Euvichol-Plus reduces the vial's volume by nearly 30 percent and weight by over 50 percent, allowing easier transport and distribution of the vaccine and waste management. Compared with glass vials, the plastic packaging is also easier to open and administer.

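### The printed assumptions do not give 90% power with 186 evaluable subjects per arm, and the 70% reference rate is above the protocol's own Indian post-second-dose averages

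*Supplement*

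**What the plan says.** The sample-size paragraph appears in section 6.2 and, in the same terms, in the synopsis (section 3.0). It cites a published study of the two vaccines with rates "14 days after first and second dose of vaccine ranges from 73% to 90% in adults and children. Assuming seroconversion rate of 70" per cent. The design inputs are "Assuming seroconversion rate of 70% in the reference arm, power of 90%, alpha of 5% (2-sided) and a non-inferiority margin of 10" per cent. From these it derives 186 subjects per arm, raised to 208 per arm (416 in total) for 10% dropout, half adults and half children. No test-arm rate or true difference is given in either place.

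The primary endpoint (section 4.8) is seroconversion to O1 Ogawa and Inaba two weeks after the second dose. Section 6.1 places the study in an Indian population. Section 4.0 reports Indian results for Shanchol and the same reformulated vaccine:

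- Vellore adults: "Seroconversion rates after the first and second dose in adults were 67.7% and 55.2%, respectively, against O1 Inaba; 47.9% and 45.8% against O1 Ogawa".
- Vellore children: "80.2% and 68.8%, respectively, against O1 Inaba; 72.9% and 67.7% against O1 Ogawa".
- Kolkata placebo-controlled study: "The rates of seroconversion after the second dose were found to be 46% of adults and 82% of children".
- Kolkata five-year-interval trial, mixed ages: "Seroconversion rates were 66% and 69% following two-dose regimens in the boosting and primary immunization arms".

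Section 6.2 uses none of these figures.

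**The concern.** For a non-inferiority comparison of proportions, sample size depends on the assumed rate in each arm, because together they fix both the variance and the distance from the margin. The plan gives only one rate. A reader would take the usual default, that the vaccines are truly equal, and would then believe that equal vaccines have a 90% chance of showing non-inferiority.

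The 70% also looks cautious because it lies below a 73–90% range. But that range covers both post-dose time points, while the endpoint concerns only the second. In Vellore every O1 rate was lower after the second dose than after the first. Lower rates lie nearer 50%, where the binomial variance is largest.

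The synopsis calls this a pivotal Phase III study, and it is meant to support licensure in India. If the real power is much lower than stated, a failed or inconclusive result could be read as a deficit of the test vaccine when the cause is limited precision.

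**Working it through.** **Inputs (section 6.2).** Reference rate pR = 0.70; margin 0.10; two-sided 5% alpha, that is 2.5% one-sided (z = 1.960); power 90% (z = 1.282); 1:1 allocation; n = 186 evaluable per arm. The test-arm rate pT is not stated.

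**Formulas (unpooled variance, unstratified).**

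V = pR(1 − pR) + pT(1 − pT)

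n per arm = (1.960 + 1.282)² × V / (0.10 + pT − pR)² = 10.507 × V / (0.10 + pT − pR)²

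Power = Φ[(0.10 + pT − pR) / √(V/n) − 1.960]

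**Step 1. Try to reproduce 186.**

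- Equal rates, 0.70 and 0.70: V = 0.42; n = 10.507 × 0.42 / 0.01 = 441.3, so 442.
- One-sided 5% alpha with 90% power gives 360. At 80% power the results are 330 (one-sided 2.5%) and 260 (one-sided 5%). None is 186.
- pT = 0.75: V = 0.21 + 0.1875 = 0.3975; n = 10.507 × 0.3975 / 0.0225 = 185.6, so 186. This matches exactly.
- Equal rates of 90% give 190, which is close but contradicts the stated 70%.

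The dropout step is sound: 186/0.9 = 206.7, in line with 208 per arm.

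**Step 2. Power of 186 per arm at the stated 70%.**

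- Equal vaccines: √(0.42/186) = 0.0475; 0.10/0.0475 = 2.104; Φ(0.144) = 55.7%. If all 208 per arm were evaluable it would be 60.5%.
- Test vaccine 5 points better: √(0.3975/186) = 0.0462; 0.15/0.0462 = 3.245; Φ(1.285) = 90.1%.

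The unstated 5-point advantage is therefore worth 90.1 − 55.7 = 34.4 points of power.

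**Step 3. Indian post-second-dose reference rates (section 4.0).** Adults and children are weighted 1:1, as in the planned cohorts:

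- Vellore Ogawa: (45.8 + 67.7)/2 = 56.75%
- Vellore Inaba: (55.2 + 68.8)/2 = 62.0%
- Kolkata placebo-controlled study: (46 + 82)/2 = 64.0%
- Kolkata five-year-interval trial: 66% (boosting) and 69% (primary immunization), as reported for mixed ages

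| Reference rate | Power, equal rates | Power, test +5 points | n per arm for 90%, equal | n per arm for 90%, +5 |
|---|---|---|---|---|
| 70% (plan) | 55.7% | 90.1% | 442 | 186 |
| 69% | 55.0% | 89.4% | 450 | 190 |
| 66% | 53.0% | 87.7% | 472 | 201 |
| 64% | 52.0% | 86.6% | 485 | 208 |
| 62% | 51.1% | 85.7% | 496 | 214 |
| 56.75% | 49.5% | 83.8% | 516 | 225 |

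The lower reference rate costs between 0.7 points (at 69%) and about 6 points (at 56.75%) in either column.

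**Step 4. Within-cohort variance.** Here V is averaged over the two age cohorts instead of being computed from the averaged rate. At +5 points the power is 86.4% (Vellore Inaba), 85.6% (Vellore Ogawa) and 91.3% (Kolkata 46%/82%). The loss is smaller for Vellore and disappears for the Kolkata split.

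**The case against.** The strongest reply is that choosing among imperfect prior estimates is planning judgment. The authors placed 70% three points below the range from a study of these two vaccines, children in one Kolkata study reached 82%, and 69% is only one point away. Randomization is stratified by age with fixed cohorts, so within-cohort variance is a natural basis, and on it one of the Indian sources gives more than 90% at +5 points. All of this stands, and it makes the reference rate a secondary matter. None of it explains 186, which does not follow from the printed inputs at any of the usual alpha and power conventions.

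Several stronger readings are tempting but not supported:

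- *That the 70% rate is the main reason why 90% is overstated.* It costs at most about 6 points; the missing test-arm rate accounts for about 34.
- *That power is below 90% whatever the true difference.* A 10-point advantage gives about 98% at both 62% and 56.75%.
- *That 70% was derived from the 73–90% range.* It lies below that range, and no derivation is given.
- *That the range is known to come from outside India.* Section 6.2 names no country. Section 4.0 says of the manufacturer's Shanchol-controlled trial: "This trial was conducted in the Philippines and immunogenicity testing was performed at the IVI labs in Seoul". It gives no rates for that trial, so the link is an inference.
- *That an averaged rate below 70% always lowers power.* The Kolkata split under within-cohort variance shows otherwise.

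**Conclusion.** The stated 90% power is not supported by the stated inputs. If the vaccines are truly equal at 70%, 186 evaluable per arm gives about 56% power, and 90% would need 442 per arm (492 with 10% dropout). The printed 186 matches a test vaccine 5 points better than the reference, an assumption the documents do not state.

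Secondarily, 70% is supported only by a range that mixes time points, and it is above every Indian post-second-dose O1 or overall average in section 4.0. Over those averages, power is 49.5–55.0% with equal vaccines and 83.8–89.4% with a 5-point advantage.

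These figures rest on unpooled variance, one-sided 2.5%, an unstratified comparison and 1:1 weighting of adults and children. The 66% and 69% come from mixed ages (6–14 and over 15 years) with an unknown split, and the 66% from a boosting arm. The synopsis names chi-square or Fisher's exact tests and does not say whether the non-inferiority comparison is stratified by cohort. If the endpoint requires a rise to both Ogawa and Inaba, the Vellore rate could not exceed 56.75%.

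**What to change.** In section 6.2 and the synopsis:

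1. State the test-arm seroconversion rate, or the true difference, that was assumed, and justify it.
2. Cite the Indian post-second-dose rates from section 4.0 as the basis for the reference arm: 56.75% (Vellore Ogawa), 62.0% (Vellore Inaba) and 64% (Kolkata), each averaged 1:1, and 66–69% as reported for mixed ages.
3. Replace 90% with the power that 186 evaluable per arm gives across those rates: about 50–55% with equal vaccines (55.7% at 70%) and about 84–89% if the test vaccine is truly 5 points better. Say that these are unstratified figures.

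Enrolment stays at 416 and no subject is added. The work is rewording one paragraph in two places. The only downside is a less favourable stated power.

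### The planned 186 per arm gives 90% power only if Euvichol-Plus seroconverts at about 75% against 70% for Shanchol, a rate the protocol does not state; at equal 70% rates power is about 56%

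*Supplement*

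**What the plan says.** Section 6.2 (Sample Size) sets out the calculation: "Assuming seroconversion rate of 70% in the reference arm, power of 90%, alpha of 5% (2-sided) and a non-inferiority margin of 10%, 186 subjects" in each arm. The Sample Size Justification row of the protocol summary (section 3.0) repeats it: "186 subjects would be required in the test and reference arms to establish non-inferiority of the vaccine". Both places then allow for 10% dropout and enrol 208 per arm, 416 in total.

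The one rate assigned to an arm is the reference rate: "Assuming seroconversion rate of 70% in the reference arm". No true rate for Euvichol-Plus, and no assumed difference between the vaccines, appears in either place or elsewhere in the protocol. The sentence before the calculation says that published seroconversion with Shanchol and Euvichol "ranges from 73% to 90% in adults and children". That range pools both vaccines, both doses and both age groups, and is not allotted to either arm.

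**The concern.** A two-arm non-inferiority calculation on proportions needs two true rates. When only the reference rate is given, the customary reading is that the test product is assumed equal to it. On that reading 186 per arm is far too few for the stated 90% power.

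Equality is also the case the protocol's own description suggests. Section 4.2 lists the same five inactivated strains in the same amounts for both products, section 4.6 describes their composition as similar, and section 4.0 reports comparable vibriocidal responses in the earlier Philippine comparison. No part of the protocol argues that Euvichol-Plus seroconverts more often.

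This calculation is the only justification for the size of a pivotal licensure trial. If the vaccines are equal at 70%, a truly equivalent vaccine would miss non-inferiority about 44% of the time (1 - 0.557), not 10%.

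**Working it through.** **Inputs from section 6.2:** reference rate pR = 0.70; margin M = 0.10; two-sided alpha 5%, so z = 1.960; power 90%, so z = 1.2816; 186 evaluable per arm; 208 enrolled per arm. Allocation is 1:1 (section 6.4).

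**Assumptions that the protocol does not supply:** non-inferiority is shown when the lower limit of a two-sided 95% confidence interval for (test minus reference) lies above -10 points, and the primary endpoint is a single yes/no outcome per subject.

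**Formula.** n per arm = (1.960 + 1.2816)² × [pT(1-pT) + pR(1-pR)] / (pT - pR + M)², where (1.960 + 1.2816)² = 10.507.

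**Step 1: reproduce 186.**
- Equal rates, pT = 0.70: 10.507 × (0.21 + 0.21) / 0.10² = 441.3, so 442 per arm. This is not 186.
- pT = 0.75: 10.507 × (0.1875 + 0.21) / 0.15² = 185.6, so 186 per arm. This matches.
- Solving backwards for the test rate that gives 90% power with n = 186 and pR = 0.70 returns 74.99%.

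**Step 2: other readings at equal 70% rates.**

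| Reading | n per arm |
|---|---|
| Two-sided 5%, 90% power, Farrington-Manning variance | 441 |
| Two-sided 5%, 90% power, pooled variance | 442 |
| One-sided 5%, 90% power | 360 |
| Two-sided 5%, 80% power | 330 |
| One-sided 5%, 80% power | 260 |

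None gives 186.

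**Step 3: dropout.** 186 / 0.9 = 206.7, so 207 per arm against the stated 208. This step is sound to within rounding.

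**Step 4: power with 186 evaluable per arm.** Power = Φ[(pT - pR + 0.10)/SE - 1.960], with SE = √{[pT(1-pT) + pR(1-pR)]/186}.
- 70% vs 70%: SE = √(0.42/186) = 0.04752; 0.10/0.04752 - 1.960 = 0.144; power 55.7%. Simulation gives 55.9%, and an exact calculation with a Newcombe interval 56.6%.
- 75% vs 70%: SE = √(0.3975/186) = 0.04623; 0.15/0.04623 - 1.960 = 1.285; power 90.1%.
- 70% vs 70% with all 208 per arm evaluable: SE = √(0.42/208) = 0.04494; power 60.5%.

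| True Euvichol-Plus rate (reference 70%) | Power, 186 per arm |
|---|---|
| 70% | 56% |
| 71% | 64% |
| 72% | 72% |
| 73% | 79% |
| 74% | 85% |
| 75% | 90% |

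**Step 5: equal true rates other than 70%, 186 per arm.**

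| Both rates | Power |
|---|---|
| 57% | about 50% |
| 70% | 56% |
| 73% | 58% |
| 80% | 67% |
| 90% | 89.5% |

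The 57% row is the adult and child average of the post-second-dose Ogawa rates in the Vellore study in section 4.0: (45.8 + 67.7)/2 = 56.75. The 73% and 90% rows are the ends of the published range in section 6.2.

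**The case against.** The best defence is that 186 is not a miscalculation: it is the right answer for 75% vs 70%. That stands. Strictly, the stated inputs do not determine n, and the figure of 442 rests on the convention that an omitted test rate means equal rates. The defect is a missing assumption on which the power claim depends, not a slip in arithmetic. It also stands that 75% is an inference from the match and is nowhere documented.

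A second defence is that equal rates above 70% would raise power, and section 6.2 itself cites 73% to 90%. This is true, but it helps only near the top of that range: 58% power at 73%, 67% at 80%, and close to the claim only at 90%. The plan chose 70%.

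A third is that the protocol states no confidence-interval rule. The synopsis names a Yates-corrected chi-square or Fisher's exact test, and section 12.0 a threshold of p < 0.05. The power figures above therefore rest on an assumed rule. It is the usual counterpart of a two-sided 5% alpha with a 10-point margin, and it is the rule under which 186 can be reproduced. Reading alpha as one-sided 5%, against the text, still gives only 68% at equal 70% rates.

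A reader might go further and infer that 70% is too high for India. The documents are mixed. Post-second-dose O1 rates at Vellore run from 45.8% to 68.8% and Kolkata adults reached 46%, but Kolkata children reached 82% and a primary two-dose arm 69%. Against the cited 73% to 90%, 70% is cautious. Nor do the documents show that any regulator or ethics committee was misled; the summary of changes records only that the margin, and the sample size with it, were revised on a committee's recommendation.

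**Conclusion.** The point holds. As written, section 6.2 and the synopsis claim 90% power from inputs that do not produce it unless an unstated Euvichol-Plus rate of about 75% is added. At the plan's own 70% for both vaccines, power is about 56% with 186 evaluable per arm and about 60% with all 208. Reaching 90% there would take 442 evaluable per arm.

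These sizes assume the 95% confidence-limit rule, a single binary endpoint and the pooled adult and child comparison. It does not follow that the trial must be enlarged, or that it is underpowered whatever the true rates are: power depends on rates not yet known, and 416 may be a defensible choice. What cannot stand is an unconditional 90% resting on a 5-point advantage that the protocol neither states nor supports.

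**What to change.** Keep 416 subjects. In section 6.2 and in the Sample Size Justification of the synopsis:

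- State the assumed true Euvichol-Plus rate and justify it. The sponsor should confirm the value actually used; 186 corresponds to 75% vs 70%.
- Replace the unconditional 90% with power at 186 per arm against a 70% reference: 56%, 64%, 72%, 79%, 85% and 90% for true test rates of 70% to 75% in one-point steps.
- Add power at equal rates over a plausible range: about 50% at 57%, 58% at 73%, 67% at 80% and 89.5% at 90%.
- State the success rule on which these figures rest.

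The cost is a protocol text change in two places, with no extra subjects and no change to the design. The stated power becomes less favourable.
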